## Abstract

Permanent cardiac pacing is the only available therapy in patients with atrioventricular (AV) conduction disorders and can be lifesaving. However, conventional right ventricular pacing (RVP) causes dyssynchronous electrical and mechanical activation of the ventricles, possibly resulting in pacing-induced cardiomyopathy and heart failure. Left bundle branch area pacing (LBBAP) might overcome these adverse effects of RVP, but evidence to support this assumption is lacking. The LEAP trial is a multi-centre investigator-initiated, prospective, randomized controlled, open-label, blinded endpoint evaluation (PROBE) study, designed to test the hypothesis that in patients with an indication for pacemaker implantation due to AV conduction disorders with an expected ventricular pacing percentage ≥20%. LBBAP is superior to RVP in preventing the composite primary endpoint of (1) all-cause mortality, (2) hospitalization for heart failure, and (3) a more than 10% point decrease in left ventricular ejection fraction (LVEF) leading to an LVEF below 50%. The LEAP trial randomizes 470 patients 1:1 to the index LBBAP or RVP control arm. The primary endpoint will be determined at 1-year follow-up. This article describes the design and analytic plan for the trial.

## Introduction and rationale

Permanent cardiac pacing is the only available therapy in patients with bradycardia because of atrioventricular (AV) conduction block. For decades, the standard approach for permanent cardiac pacing has been right ventricular pacing (RVP). However, RVP results in a non-physiologic, dyssynchronous ventricular activation.^1–4^ This dyssynchronous activation may lead to a pacing-induced cardiomyopathy in up to 36%^5^ of patients, possibly leading to heart failure in the long run.^2,5–8^

Left bundle branch area pacing (LBBAP) has been proposed as a more physiologic pacing approach than conventional RVP. Several LBBAP entities have been distinguished, consisting of left ventricular septal pacing (LVSP), left bundle branch pacing (LBBP), and left bundle fascicular pacing (LBFP).^9^ Although in theory capture of the left-sided Purkinje system (LBBP and LBFP) provides the most physiological left ventricular (LV) activation, a substantial amount of patients end up being treated with LVSP.^10^ In animal studies, short- and long-term LVSP has been shown to maintain regional cardiac mechanics, contractility, relaxation, and efficiency, whereas RVP diminished these variables.^11,12^ A large European multi-centre registry demonstrated the feasibility and safety of LBBAP as a primary pacing technique in bradyarrhythmias.^13^

Although LBBAP provides a novel, theoretically more physiological and synchronous pacing approach than traditional RVP, and non-randomized and small randomized studies suggest the potential for clinical benefits from this pacing approach,^6,13–18^ to our knowledge, no large randomized clinical trial (RCT) has yet been performed. We describe here the design of the LEAP trial, a multi-centre randomized controlled trial comparing the effects of LBBAP with RVP in patients with AV block.

### Study design

The LEAP trial is a multi-centre investigator-initiated, prospective, randomized controlled, open-label, blinded endpoint evaluation (PROBE) trial, which is designed to test the hypothesis that LBBAP is superior to the current standard of care with RVP.

Patients who meet the inclusion and exclusion criteria (*Table 1*) are randomized in a 1:1 ratio to LBBAP or RVP after signing informed consent. The study was approved by the medical ethical committee of the Maastricht University Medical Center, the Netherlands (METC 20–029). The LEAP trial is registered at www.clinicaltrials.gov (NCT 04595487). The Trial design is provided in *Figure 1*.

**Figure 1 oeag108-F1:**
[figure not shown]
Trial design. PM, pacemaker; LBBAP, left bundle branch area pacing; RVP, right ventricular pacing; TTE, transthoracic echocardiogram. *TTE was only performed at baseline and 12 months follow-up.

**Table 1 oeag108-T1:** Inclusion and exclusion criteria of the LEAP study

Inclusion criteria	Exclusion criteria
Age ≥ 18 years Life expectancy with good functional status of ≥ 1 year Class I or IIa PM indication due to AV conduction disorder Acquired third or second degree AVB Atrial arrhythmia with slow ventricular conduction Expected VP percentage ≥ 20% LVEF ≥40% on TTE ≤ 3 months before PM implantation Signed and dated ICF	HF NYHA classes III and IV Class I indication for CRT Class I indication for ICD Previous implanted CIED (except for ILR) Atrial arrhythmia with planned AV junction ablation ACS or unstable angina PCI or CABG ≤30 days before enrollment VHD with indication for valve repair or replacement HCM with IVS thickness > 2 cm
	Renal insufficiency requiring HD Active infectious disease or malignancy Pregnancy

ACS, acute coronary syndrome; AV, atrioventricular; AVB, atrioventricular block; CABG, coronary artery bypass graft; Class I, pacemaker implantation is indicated^19^; CIED, cardiac implantable electronic device; Class IIa, pacemaker implantation should be considered^19^; CRT, cardiac resynchronization therapy; HCM, hypertrophic cardiomyopathy; HD, haemodialysis; HF, heart failure; ICD, implantable cardioverter defibrillator; ICF, informed consent form; ILR, implantable loop recorder; IVS, interventricular septum; LVEF, left ventricular ejection fraction; NYHA, New York Heart Association classification; PCI, percutaneous coronary intervention; PM, pacemaker; VHD, valvular heart disease; VP, ventricular pacing.

### Patient population

The trial is performed in adult patients with a permanent pacing indication because of AV block (class I or IIa according to the 2021 ESC guidelines^19^) with an expected ventricular pacing percentage of ≥ 20% and a left ventricular ejection fraction (LVEF) ≥ 40%. Inclusion and exclusion criteria are provided in *Table 1*.

### Randomization, blinding, and treatment allocation

Patients are randomized in a 1:1 ratio via an interactive response technology system by block randomization. Random permuted block sizes will be used to prevent prediction of treatment allocation before randomization. Randomization will be stratified by sex and percentage of LVEF (i.e. LVEF <50% and LVEF ≥50%) to ensure an even distribution of these characteristics between the two treatment groups. Given the nature of the treatment arms, the participating patients and treatment team are not blinded. Adjudication of the endpoints is performed by a blinded committee.

## Study procedures

### Intervention group

The intervention group is treated with LBBAP. LBBAP consists of the implantation of a pacemaker with the ventricular lead delivered through the interventricular septum to the LV septum, targeting capture of the LBB. However, if it is not possible to capture the LBB, LVSP is considered adequate as well.^9^ The feasibility and safety of this implantation method have been described previously.^13,14,20^

In case of unsuccessful lead positioning in the LBBAP region, the lead may be placed at the His bundle region or in the right ventricle according to the physician’s discretion.

### Control group

The control group is treated with RVP (current standard of care). The ventricular pacing lead is placed in the RV according to the routine of the implanting physician.

### Diagnostic work-up and follow-up

The diagnostic work-up prior to pacemaker implantation includes recording of medical history and medication use, physical examination, 12-lead ECG, and a baseline transthoracic echocardiogram (TTE) no longer than 3 months before pacemaker implantation. Patients will be followed until the last included patient reaches the 1-year follow-up mark.

Pacemaker check-ups following the intervention are performed at 1 month (±2 weeks), 6 months (±2 months), 12 months (± 2 months), and thereafter every 6 months. VVI-paced 12-lead ECG recordings, electrical lead measurements (including sense, threshold, and impedance for all the implanted leads), percentage of ventricular pacing, and atrial high rate episodes (AHRE)/atrial fibrillation (AF) episodes lasting more than 24 h are collected during these checks.

All patients visit the physicians’ outpatient clinic at 6 (±2 months) and 12 months (±2 months) after pacemaker implantation and every 6 months thereafter (follow-up at 18 and 30 months may be performed as a remote visit, i.e. phone consultation) until a maximal follow-up of 36 months. The occurrence of adverse medical events, death, hospitalization (for heart failure), AF, pacemaker-related complications, and New York Heart Association classification (NYHA) class will be noted during these visits. An additional check of adverse events and endpoints will be performed after the last included patient reaches the 1-year follow-up mark.

In addition to the baseline TTE prior to pacemaker implantation, a follow-up TTE is performed at 1 year after implantation. LVEF is determined according to the modified Simpson’s method. Moreover, LV dimensions, the presence of valvular abnormalities, and diastolic function are graded. Diastolic function will be assessed by determining the following echocardiographic parameters at baseline and 1-year follow-up: E-wave, A-wave, E/A ratio, septal and lateral e’, E/e’, 2D-strain of the left ventricle and atrium, pressure gradient across the tricuspid valve, and volume of the left atrium. Diastolic function will be graded according to the recommendations by Nagueh et al.^21^ Diastolic dysfunction assessment will be limited by the presenting rhythm at baseline echocardiography.

At baseline and every 6 months thereafter until the end of the study, the EQ-5D-5L questionnaire is used to assess health-related quality of life (QOL), and the iMTA Productivity Cost and iMTA Medical Consumption Questionnaire are used for the calculation of costs outside of the hospital.

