### Secondary endpoints

Secondary endpoints are:

Time to first occurrence of all-cause mortality or hospitalization for heart failure.Time to first occurrence of all-cause mortality.Time to first occurrence of hospitalization for heart failure.Time to first occurrence of AF *de novo* and AF burden at every follow-up visit.The echocardiographic change in LVEF at 1 year as compared to baseline.The echocardiographic changes in diastolic (dys-)function at 1 year as compared to baseline.The occurrence of pacemaker-related complications.QOL assessed by the EQ-5D-5L questionnaire.Cost-effectiveness analyses and budget impact analysis (BIA).

The secondary endpoints (other than echocardiographic endpoints) will be determined at the end of the follow-up period when the last included patient has reached 1-year follow-up. The individual follow-up time for patients at this time point will vary, with a minimum of 1 year and a maximum of 36 months.

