### Adjudication of endpoints

All clinical endpoints as described above are adjudicated by an independent, blinded endpoint adjudication committee (EAC). The EAC consists of three experienced cardiologists. Two of them adjudicate all clinical endpoints. In case of disagreement, after discussion with the third committee member, they decide on the adjudication of the endpoint. All endpoints are adjudicated using standardized definitions provided in the EAC charter.

An independent echo core lab, composed of two experienced imaging cardiologists, assesses all baseline and follow-up TTE’s. Based on the baseline and 1-year follow-up LVEF, as assessed by the echo core lab, the echocardiographic part of the primary endpoint is determined. The echo core lab is blinded for the study number and date of the examination. Due to the presence of pacing leads, the core lab cannot be completely blinded to the allocation of the patient.

An ECG core lab, consisting of two experienced LBBAP implanters, assesses all paced baseline and 1-year follow-up ECG’s to determine the presence of RVP, deep septal pacing, or LBBAP according to the previously published definition.^9^ Capture of the left-sided Purkinje system is determined according to the current consensus.^9^

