## Analyses

### Sample size calculation

Based on previously reported mortality, heart failure hospitalizations, and significant deterioration of LVEF,^2,6–8,22^ we estimate that the proportion of patients in the RVP group that will develop any of the composites of the primary endpoint before 1-year follow-up will be at least 25%. We expect an event rate of 14% for the LBBAP group. Event rates are based on the effect size of heart failure-related events by his pacing in those with ventricular pacing percentage >20%.^6^ When designing this trial, no data on event rates in LBBAP were available yet. The effect size of LBBAP was estimated to be equal to HBP when designing this trial. To achieve a power of 80% at the 5% level of significance, 203 patients per group, or 406 in total, would be needed. Accounting for around 15% loss to follow-up or patients not receiving the allocated intervention, 470 patients are needed.

After designing the trial, Sharma et al. reported an occurrence of the combined primary clinical endpoint of mortality, heart failure hospitalization, or upgrade to CRT among patients with ventricular pacing burden > 20%, in 26.1% in RVP and 8.4% in LBBAP after a mean follow-up of 1.5 years in a non-randomized trial (HR 0.32; 95% CI 0.19–0.54; *P* 0.001).^15^ This study included a longer follow-up duration but excluded the echocardiographic endpoint. The addition of the echocardiographic endpoint in the LEAP trial will generate more endpoints in a shorter follow-up duration. Therefore, the study by Sharma et al. is substantiating the sample size calculation.

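### AF burden is a secondary endpoint, but the only device AF data listed are episodes longer than 24 h, which cannot give AF burden as usually understood

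*Protocol article*

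**What the plan says.** In the Protocol article, Secondary endpoints, one item combines time to first new AF "and AF burden at every follow-up visit".

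Diagnostic work-up and follow-up describes three sources that bear on AF:

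- **Device memory.** Pacemaker checks take place at 1, 6 and 12 months and then every 6 months. AHRE/AF "episodes lasting more than 24 h are collected during these checks". Neither total time in AF nor any shorter episode is listed.
- **Outpatient visits** at 6 and 12 months and every 6 months after that. The items noted are given as "The occurrence of adverse medical events, death, hospitalization (for heart failure), AF, pacemaker-related complications" and NYHA class. No minimum duration is attached to AF.
- **ECGs** at the device checks: "VVI-paced 12-lead ECG recordings, electrical lead measurements".

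The article does not define AF burden or new AF. On definitions, Adjudication of endpoints says: "All endpoints are adjudicated using standardized definitions provided in the EAC charter". That charter is not shown.

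**The concern.** AF burden is ordinarily the share of time spent in AF. It needs total AF time, or all episodes with their durations. The article sets a collection rule with an explicit cut at 24 h, and that rule does not supply either. This is more than a detail left to another document: an analysis plan or a charter can define burden, but it cannot recover device data that were not collected.

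AF belongs to the trial's own rationale. The Discussion names it among the risks associated with right ventricular pacing. If burden is computed from long episodes only, a finding of no difference could be read as no effect of pacing site on AF burden, when AF in shorter episodes was never measured.

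**Working it through.** **Figures in the plan.** The article gives no AF rate, no episode durations and no power calculation for AF, so there is no AF figure to reproduce. The only design calculation is for the primary endpoint: 25% against 14%, two-sided 5%, 80% power. With pooled variance and no continuity correction this gives 203 per group and 406 in total, as stated. It has no AF input, so nothing below changes it.

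**Step 1: what each source can deliver.**

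| Source | Duration limit | Gives an amount of AF? | Can show that AF occurred? |
|---|---|---|---|
| Device episodes | longer than 24 h | only for long episodes | yes, for long episodes |
| Outpatient note | none stated | no | yes, if AF came to clinical notice |
| 12-lead ECG at device check | none | no, a snapshot | yes, if AF is present and recognised at that moment |

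Only the first row carries a quantity, and it is truncated. For burden, the other two rows cannot fill the gap. For new AF they can fill part of it.

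**Step 2: effect of the truncation on burden.** Inputs: an interval of 182.5 days (half a year, matching the 6-monthly checks), which is 182.5 × 24 = 4,380 h. The episode patterns are assumptions chosen to show the arithmetic.

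True burden = (number of episodes × hours per episode) / 4,380. Captured burden = the same sum over episodes longer than 24 h only.

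| Assumed pattern | Hours in AF | True burden | Captured burden |
|---|---|---|---|
| 30 episodes of 6 h | 180 | 4.1% | 0% |
| 30 episodes of 12 h | 360 | 8.2% | 0% |
| 60 episodes of 23 h | 1,380 | 31.5% | 0% |
| 1 episode of 25 h | 25 | 0.57% | 0.57% |

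Comparing the last two rows, the third patient has 1,380 / 25 = 55 times as much AF as the fourth, yet scores lower. The truncation therefore understates the level and can also reverse the order of patients.

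**Step 3: effect on new AF.** An episode of 24 h or less enters time to first new AF if it is noted at an outpatient visit or seen on an ECG. If it is known only from device memory, nothing listed brings it into the data. The clinical route is open-label, since patients and treating teams know the allocation (Randomization, blinding, and treatment allocation), and the 18- and 30-month visits may be remote. Blinded adjudication acts on events that are reported; it does not find those that are not.

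**The case against.** The strongest reply is that this is a condensed article. AF burden is not defined in it, definitions are assigned to the adjudication charter, and a 24 h threshold may be deliberate. That stands as far as it goes: a threshold is a legitimate choice. But if burden means AF in episodes above 24 h, the endpoint's name should say so, and if it means time in AF, the listed data do not provide it. Either way the two sections need to be reconciled.

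A reader might infer several stronger things that the article does not support:

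- *That shorter episodes are scored as zero.* No section says how they are scored. The text shows only that they are not listed as collected from the device.
- *That new AF is invisible until an episode passes 24 h.* The outpatient note has no duration limit, and ECGs are taken at device checks.
- *That most patients with paroxysmal AF would be counted as AF-free, or that power for an AF effect is lost.* Neither can be computed without AF rates or durations, and the article gives none.
- *That the comparison between arms is biased.* The same threshold applies to both arms. It changes what is measured and can hide a difference in shorter AF, but it does not by itself favour one arm. Open-label noting of short episodes makes unequal ascertainment possible; nothing shows that it occurs.

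It is also fair to say that the article does not describe what the devices store, so a cumulative counter may not be available for every patient. The fix allows for that.

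**Conclusion.** The mismatch is real and confined to one secondary endpoint. As listed, the device data cannot give AF burden in the sense of time spent in AF; they give at most the part lying in episodes longer than 24 h. For new AF the gap is narrower: it concerns device-detected episodes of 24 h or less that are not also noted clinically or on an ECG.

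The size in this trial is unknown. The worked cases (31.5% true burden captured as 0%, against 0.57% captured in full) show what the rule can do and do not estimate how often it happens. The conclusion rests on three assumptions: that burden carries its ordinary meaning, that the 24 h limit applies to AHRE and AF alike, and that the list of data taken at device checks is complete as regards AF. If the full protocol or the charter shows otherwise, aligning the wording is enough. The primary endpoint and the sample size are untouched. The change is worth making because it is cheap and determines what can be concluded about AF.

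**What to change.** State the definition of AF burden and of new AF, with any duration threshold, and make the data collection match:

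1. At each scheduled device check, also record cumulative AT/AF time as a percentage of the time since the previous check, and the date and duration of the first AHRE, where the device provides them.
2. Define AF burden from that counter, and keep episodes longer than 24 h as a separate measure.
3. Where the counter cannot be retrieved, rename the endpoint as AF episodes longer than 24 h, or burden from such episodes, and report it under that name.

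The first two steps cost one or two extra data fields per check, at checks already planned. The third is a change of wording. None of them touches treatment, the visit schedule or the primary analysis.

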## Endpoints

### Primary endpoint

The primary endpoint is the composite of all-cause mortality, hospitalization for heart failure, and a more than 10%-point decrease in LVEF leading to an LVEF below 50%, which as a binary combined endpoint will be determined at 1-year follow-up.

Heart failure hospitalization is defined as:

Hospitalization or unplanned hospital visits for heart failure requiring intravenous diuretics and/or (adjustment) of other medical heart failure therapy.Or hospitalization for upgrade to cardiac resynchronization therapy (CRT) (biventricular pacing) for progression of heart failure with worsening NYHA class and/or (increased) need for diuretic therapy or other medical heart failure therapy.Or hospitalization for upgrade to CRT for developing a class I indication for CRT.Or hospitalization or unplanned hospital visit for heart failure triggered by an episode of atrial fibrillation with uncontrolled heart rate requiring intravenous diuretics or adjustment of rate control therapy.

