### Limitations

Due to the chosen design, this trial has several limitations. The composite primary endpoint consisting of both clinical outcomes (death and heart failure hospitalization) and echocardiographic outcome (a more than 10% point decrease in LVEF leading to an LVEF below 50%) has some limitations. First, due to limited data on outcomes in LBBAP regarding mortality, heart failure hospitalization, and echocardiographic changes when compared to RVP, it is unclear how much each part of the composite endpoint will contribute to the overall result. Based on previous reports,^16,17^ the echocardiographic part is expected to contribute for ∼50% or more to the primary endpoint. Second, due to the addition of an echocardiographic endpoint, no time-to-event analysis is possible for the primary endpoint. Therefore, secondary endpoints with time-to-event analyses are added to the protocol.

Moreover, the sample size calculation for the study is mostly based on a study on HBP^6^ because effect sizes for LBBAP were largely unknown when designing this trial. Due to the limited available data and no prospective, retrospective, or randomized studies available on the combined endpoint chosen in this trial, the sample size calculation is based on an estimation. This might result in a less accurate sample size calculation.

Nevertheless, choosing a composite endpoint including only clinical outcomes (i.e. death and heart failure hospitalization) would require a much larger sample size and longer follow-up duration. LBBAP is currently applied on a large scale in routine clinical care without evidence from large, randomized trials. Due to the need for randomized data on LBBAP on a shorter term, the current design was chosen.

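### Pacing upgrades count as heart-failure events only if they are to biventricular CRT, so the same deterioration treated by revision to LBBAP or HBP can be scored event-free

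*Protocol article*

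**What the plan says.** Under Primary endpoint, the protocol article defines a composite of death, heart-failure hospitalization and LVEF decline, "which as a binary combined endpoint will be determined at 1-year follow-up". Four criteria define heart-failure hospitalization. Two concern upgrades: "hospitalization for upgrade to cardiac resynchronization therapy (CRT) (biventricular pacing) for progression of heart failure with worsening NYHA class" (and/or an increased need for diuretics or other heart-failure drugs), and "hospitalization for upgrade to CRT for developing a class I indication for CRT". The first equates CRT with biventricular pacing, and the second does not redefine it. Neither mentions revision to LBBAP or HBP.

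A revised patient could still be caught by the general criterion, "Hospitalization or unplanned hospital visits for heart failure requiring intravenous diuretics and/or (adjustment) of other medical heart failure therapy", by the similar criterion for heart failure triggered by atrial fibrillation, or by the echocardiographic component. On the latter, Adjudication of endpoints states: "Based on the baseline and 1-year follow-up LVEF, as assessed by the echo core lab, the echocardiographic part of the primary endpoint is determined". The Figure 1 legend confirms that "TTE was only performed at baseline and 12 months follow-up".

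Under Statistical analyses, patients are analysed as randomized, and the pacing type found by the ECG core lab is only described. The treatment team is unblinded (Randomization, blinding, and treatment allocation). Limitations notes that "LBBAP is currently applied on a large scale in routine clinical care without evidence from large, randomized trials".

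**The concern.** The upgrade criteria exist to capture patients whose heart function has worsened enough to need a different pacing system. Restricting them to one device ties the event to the operator's choice rather than to the patient's condition. In a trial of LBBAP, with LBBAP in wide routine use, revision to a conduction-system lead is an obvious alternative to a biventricular system for a patient who deteriorates on RVP. If that revision also restores LVEF before the 12-month echocardiogram, the echocardiographic component no longer detects the deterioration.

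At stake are power and the size of the estimated effect, since lost events would probably fall mainly in the RVP arm. The two secondary endpoints that include heart-failure hospitalization have no echocardiographic component to fall back on. They also run for up to 36 months, which leaves more time for revisions.

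**Working it through.** **1. Scoring side by side.** Take two RVP patients, both with heart failure progressing and a worse NYHA class before 1 year. Both are admitted electively for a new pacing system, have no intravenous diuretics and no unplanned visit, and are alive at 1 year. Their 12-month LVEF no longer meets the criterion (a fall of more than 10 points to below 50%).

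| Criterion | Biventricular upgrade | Revision to LBBAP or HBP |
|---|---|---|
| Death | no | no |
| General heart-failure admission or visit | not clearly met | not clearly met |
| Upgrade with worsening heart failure | **met** | not met as printed |
| Upgrade for class I CRT indication | not needed | not met as printed |
| Heart failure triggered by atrial fibrillation | no | no |
| LVEF at 12 months | no | no |
| Score | event | event-free |

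The same contrast arises for a patient who develops a class I CRT indication and receives a conduction-system lead instead.

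**2. The plan's own sample size.** Inputs from Sample size calculation: 25% (RVP), 14% (LBBAP), 5% significance, 80% power. Sidedness is not stated; two-sided reproduces the figure. With the pooled variance under the null and p̄ = (0.25 + 0.14)/2 = 0.195:

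n = [1.96·√(2·0.195·0.805) + 0.8416·√(0.25·0.75 + 0.14·0.86)]² / 0.11² = (1.098 + 0.467)² / 0.0121 ≈ 202.5, so 203 per group. This matches the article.

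**3. Effect of unscored RVP events.** The documents give no revision rate, so m, the percentage points of RVP patients wrongly scored event-free, is an assumption. With p₁ = 0.25 − m and p₂ = 0.14:

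power = Φ{[(p₁ − p₂)·√n − 1.96·√(2p̄(1 − p̄))] / √(p₁(1 − p₁) + p₂(1 − p₂))}

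Two group sizes are shown. The first is the 203 of the calculation. The second is 470/2 = 235, because all randomized patients are analysed and missing echocardiographic data are imputed. The second is an upper bound, since it uses up the allowance for loss to follow-up and non-receipt of treatment.

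| m (points) | RVP patients of 203 | Power, n = 203 | Power, n = 235 | Odds ratio |
|---|---|---|---|---|
| 0 | 0 | 80.1% | 85.5% | 0.488 |
| 1 | about 2 | 73.0% | 79.1% | 0.516 |
| 2 | about 4 | 64.7% | 71.1% | 0.545 |
| 3 | about 6 | 55.5% | 61.7% | 0.577 |

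Successive losses are 7.1, 8.3 and 9.2 points at 203, and 6.4, 8.0 and 9.4 points at 235.

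**4. Partial offset.** If unscored events in the LBBAP arm are one fifth of those in the RVP arm, power at 203 per group is 74.9%, 68.9% and 62.3% for m = 1, 2 and 3.

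**5. Plausibility of m.** Three points is 3/25 = 12% of all expected RVP events. Limitations expects about half or more of the primary endpoint to be echocardiographic. If all the unscored events came from a half share (12.5 points), 3 points would be 3/12.5 = 24% of it.

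**The case against.** The strongest reply is that the case needs several things at once. The deterioration must come to light without a scheduled echocardiogram, the lead must be revised to LBBAP or HBP before 12 months, the general heart-failure criterion must not apply, and LVEF must have recovered by the 12-month reading. The general criterion is broad: an admission for heart failure with a drug adjustment arguably qualifies whatever lead is implanted. A patient who has not recovered is still caught by the echocardiogram. All of this stands, and it limits the number of patients affected.

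The adjudication charter is not shown and may class conduction-system upgrades as CRT. That also stands, but the published definition would then need correcting to agree with it.

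The asymmetry between arms is not measured. Under Intervention group, a failed LBBAP implant may end with a lead in the right ventricle, and such patients could be missed in the same way. This offsets part of the bias.

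A reader might infer that the primary comparison is shown to be biased against LBBAP. The documents do not support that: they give no revision rate, and they do not say that participating centres would choose LBBAP for a revision. A reader might also infer that every revision or biventricular upgrade for a fall in LVEF should be a primary event. That does not follow either. Treatment is open-label, so counting elective revisions without a threshold, or substituting unscheduled echocardiograms, would let unblinded decisions create events mainly in the RVP arm. Requiring worsening heart failure or a class I indication is a defensible safeguard.

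**Conclusion.** The point holds as a flaw in the printed definition: identical heart-failure deterioration can be an event or a non-event according to the device used to treat it. The probable direction is towards no difference, resting on the article's premise that pacing-induced cardiomyopathy arises mainly under RVP. Such a bias threatens power and the effect estimate; it would not create a false claim of superiority. The loss of 6 to 9 points of power per percentage point holds for assumed rates of 1 to 3 points, with the LBBAP rate fixed at 14%. With few such revisions the effect is small.

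**What to change.** Under Primary endpoint, and in the adjudication charter if it uses the same wording, make both upgrade criteria device-neutral: upgrade or revision to biventricular pacing, LBBAP or HBP. Keep the present qualifying conditions unchanged: worsening NYHA class and/or an increased need for diuretics or other heart-failure drugs, or a newly developed class I CRT indication. State that purely technical lead revisions do not count. This concerns scoring only, not when or how a patient should be revised.

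Add one prespecified sensitivity analysis that also counts revisions made for LVEF decline alone. In it, the echo core lab reads the last clinical echocardiogram before the revision and applies the existing LVEF criterion.

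The cost is a short wording change and core-lab reading of existing echocardiograms for the patients concerned. The adjudication committee must separate heart-failure revisions from technical ones. Because the decision to revise is unblinded, the qualifying conditions must stay.
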